### Training

**Baseline survey**: The initial training will be conducted for 30 self-help - group member/ASHA/health workers to carry out the baseline survey in all thirty clusters-intervention and control. The content of the training will include rapport building, confidentiality, familiarisation with the questionnaires in both English and Malayalam (regional language) for the household, smoker, smoker’s spouse, and child, hands on training on data collection through open data kit (ODK) on a smart phone or tablet. Each day it will be downloaded in Excel and mailed/WhatsApp’d to the program coordinator. Hands on training of the COPD 6 device which measures FeV1/V6 will be given. Monitoring of indoor air pollution for particulate matter will also be explained in a two-day training programme.

### Intervention

**Intervention training of Self Help Group - Accredited Social Health Activist (SHG-ASHA):** A three-day training and sensitisation of self-help group members and ASHAs including outlining expectations in the intervention arm will be conducted. The self-help group are an arm of the Local self-government created for social empowerment, economic empowerment and women empowerment. The list is available with the local self-government and the community is also aware about its members. Similarly the ASHA is the frontline health worker and is known to all the people. Aspects of rapport building, confidentiality, tobacco and types of tobacco products, harms due to second hand smoke, how to change smoking behaviour (3 A’s), benefits of quitting, role and responsibility of ASHA and SHG, and sensitisation regarding the prevailing laws on tobacco and indoor air pollution will be discussed. They will be given a training booklet.

The cluster level consent has been obtained from the local self-government and individual consent will be obtained. Consent will be obtained during baseline survey and also before intervention at the local self-government level.

**
*Behavioural intervention*
**

*Conceptual framework*: The theoretical basis for the intervention is the socioecological model. The Social Ecological Model (SEM) is a framework for understanding the multifaceted and interactive effects of personal and environmental factors that determine behaviours, and for identifying behavioural and organizational leverage points and intermediaries for health promotion within organizations.
^
42
^ There are five nested, hierarchical levels of the SEM: individual, interpersonal, community, organizational, and policy/enabling environment (
Figure 1). The most effective approach to public health prevention and control uses a combination of interventions at all levels of the model. At the participant/individual level the self-help group women will visit homes, use the 3 A’s of Ask, Advise and Act to speak to the smokers and their spouses to bring about behaviour change. They will use a flip chart to educate the smoker and his family on the health effects of indoor smoking. At the participant level, which is the interpersonal level in SEM, the self-help group members will talk to the influencers of the smokers. Accredited Social Health Activists (ASHAs) who are the frontline health workers will support the SHGs in implementation of the intervention. At the community and organisational level influence will be brought about by educational meetings in the ward organised by the self-help group member and by the active involvement of the elected representatives of the local self-government, other formal and informal leaders. Testimonials will be shared, the elected member will endorse the idea of smoke free homes, and video clips by leading personalities from the film industry and medical professionals will be shown. At the cluster level, children in the area will also be provided awareness so that they can convey the message in a child to parent approach among the indoor smoker households. Thus it is a composite multipronged intervention delivered by the women self-help group members comprising of face to face educational sessions singly and in groups, using influencers of the tobacco smoker, and educating the children of smokers. The self-help group member and the frontline health worker (ASHA) will be pivotal in the delivery of the intervention.

**Figure 1. f1:**
[figure not shown]
Flow diagram for recruitment and follow up.

The training booklet (6-8 pages) has been developed for the ready reference of the SHG women who will deliver the intervention. The training booklet has been prepared by a team comprising a sociologist, health educator, communication specialist, community medicine expert, ASHA, and two SHG workers. The training booklet will be in an easy to understand form. The training booklet will consist of a review of the burden of the problem of tobacco, particularly smoking, the problem of second hand smoke, impact on women and children, and the use of the 3 A’s in the local language. They will also contain advice on the importance of not smoking within the home. The SHG/kudumbasree members will be partners in the development of communication material and will assist in the development of a poster, leaflet, and flip chart in order to ensure clarity, relevance, easy readability and understanding.

In the intervention clusters, an air quality monitoring committee will be formed to support the intervention. This will comprise of the SHG, ASHA, junior public health nurse (female health worker), ward councillor, and members of our team. This committee will guide the intervention. In the initial two months of the intervention the SHG-ASHA team will conduct monthly home visits for educating the smoker, spouse and others in the family on the harms of second-hand smoke using a flip chart. The circle of influencers around the smoking men will also be contacted by the members of the self-help group to provide support to quit. They will then organize a meeting of community leaders and heads of women’s groups, present data on harms of SHS, explain the rationale for establishing smoke free homes in their community, and ask for their assistance in arranging other educational meetings for community members. Two-three such educational meetings will be conducted per cluster where all the household members, particularly that of the smoking households, are encouraged to attend. These meetings will be conducted at different places in the community and doctors from the nearby primary health centres will come and talk about the harms of SHS and importance of becoming a smoke free home community. In these meetings other stakeholders, formal and informal leaders of the community, and local self- government representatives will be invited.

In the next two months home visits will be conducted to paste the smoke free home stickers or distribute the calendars and reinforce the message of not smoking within homes and to get widespread recognition of the movement. Based on the findings of the baseline survey customized messages to quit will be delivered. The SHG-ASHA combined will also communicate the results of the cotinine levels and 2.5pm to the household members. The cotinine levels among the children and women will be an especially powerful tool to motivate and influence men to quit smoking within the homes and then to quit ultimately. If they express an interest to quit, they will be referred to the nearest urban primary health center for tobacco cessation. The influencers will be contacted again to encourage the smoker to quit smoking within home and to quit. Creating a movement and making “not smoking within the house an acceptable sociocultural norm” is the objective. At the end of the intervention as part of the dissemination activity smoke free homes declaration meeting for all community members in the presence of political leaders will be conducted.

*Control arm*: The other arm will get the standard of care which would include the routine programs which are being run by the government as part of the national tobacco control program such as training of health and social workers, NGOs, school teachers, and enforcement officers; Information, Education, and Communication (IEC) activities; school programmes; monitoring of tobacco control laws; coordination with Panchayath Raj Institutions for village level activities; and setting-up and strengthening of cessation facilities including provision of pharmacological treatment facilities at district level. Periodic assessments will be done at 10 and 16 months.

Health workers will conduct end-line surveys soon after the intervention and six months after the intervention in the intervention and control arm with the same questionnaire, urinary cotinine measurement and SHS measurement with an environmental sensor. Thus the measurements will be at 6, 10 months and 16 months respectively.

### Sample size calculation

Based on previous studies we assume an ICC of 0.06.
^
43
^ To detect a minimal difference of 0.03ng/ml in cotinine levels between groups,
^
44
^ at 80% power with a two-sided alfa of 0.05, the estimated sample size was 113 indoor smokers per arm for individual randomization. Since one of the studies in the slum area of Ernakulam had found a prevalence of indoor smoking of 16% and considering slums above 100 households it is assumed that the expected number of smokers within household will be 20 per cluster with variability in clusters. Hence we estimated the sample size for unequal cluster size,
^
45
^ with a CV of 0.45 and VIF=2.4. The estimated sample size was 271 and 14 clusters per arm. Further we assumed a drop-out rate of 10%, the final sample size was rounded to 300 per arm and 15 clusters.

**
*Randomisation*
**

The trial has been registered in Clinical Trials Registry – India
CTRI/2021/06/034478.

A simple randomisation will be undertaken of the selected slums in the urban and peri-urban areas to receive intervention or not by a computer-generated random number list.

Allocation concealment: Allocation will be based on clusters and the allocation will be done after the baseline survey assessment by a statistician not directly related to the study. There is no allocation concealment. All the indoor smokers will be recruited and they will be selected before randomising clusters.

*Implementation*: Meetings will be conducted with the Kochi Corporation and District Medical Office regarding the objectives of the study. After the baseline survey, which will help to identify the indoor smokers, smoking practices, ventilation issues, and waste management practices, a simple randomisation will be undertaken of the selected slums in the urban and peri-urban areas to receive intervention or not.

The allocation sequence generation and the assignment of participants to the intervention will be carried out by the statistician and the investigators will enrol the participants.

*Blinding*: Blinding may not be possible as a lot of people are involved, local self-government officials, the investigators team, health centres, health workers, frontline workers such as the accredited social health activist, and anganwadi workers. The group of people who collect the outcome data will be blinded.

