## Methods

### Sample selection

We have used the SPIRIT protocol according to guidelines. This will be a cluster-randomized community-based trial. Clusters will be slums with a population of more than 400 or 100 households in the Kochi Corporation and adjacent peri-urban areas. 30 clusters will be selected randomly from the sampling frame of 74 slums and colonies with a population of more than 400 population from a total list of 300 slums and colonies of Kochi Municipal Corporation and adjacent areas. These will be randomly assigned by a computer-generated table to the intervention or control arm with a 1:1 allocation ratio.

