*Baseline data*: The baseline data will be presented for both clusters and individuals as the risk of chance imbalances are greater with clusters.

*Numbers analyzed*: We plan to analyze 30 clusters with at least 300 indoor smokers in each arm. The urine cotinine of the women and children will be obtained from 300 women and or children in each arm. The indoor home values of 2.5 PM will be obtained from 300 households in each arm. Similarly, the lung function values as indicated by FeV1/FeV6 will be assessed among 300 each in the intervention and control group.

*Outcomes and estimation*: The difference in mean cotinine levels among the clusters in the intervention and control group with 95% CI will be estimated. The intracluster correlation coefficient for each outcome will be reported. Adjusted estimates of clustering will also be provided. Cox’s proportional hazards will be calculated for quitting, harm reduction, blood pressure values. This is to determine the effectiveness of an intervention based on partnering with women’s SHG’s to reduce indoor tobacco smoking by measuring urinary cotinine levels.

A repeated-measures ANOVA will be used to compare the mean urinary cotinine concentration between groups, before and after intervention.

Analysis for self-reported quit rates will be assessed by a Cox proportional hazards model. Generalised linear mixed effect models will be used to test between cluster differences from baseline to each follow up period for each outcome indicator.

We will use an intention to treat approach in analysis. A multilevel model will be used for analysis using the generalized linear mixed effect model which will also adjust for individual covariates. Key variables will be measured at baseline and then compared between arms to check balance; and if both arms are unbalanced with respect to any relevant factors, which can happen given that the unit of randomization is the cluster instead of the individual, those factors will be adjusted for in the final analysis so as to address potential confounding. Analysis for SHS exposure rates and quit rates will be assessed by a Cox proportional hazards model.

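### Simple randomisation of 30 slums does not guarantee the planned 15 clusters per arm, and the allocation makes no use of location or cluster size, both known by then

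*Protocol article*

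**What the plan says.** All references are to the protocol article.

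- **Sample selection:** "30 clusters will be selected randomly from the sampling frame of 74 slums and colonies". On assignment: "These will be randomly assigned by a computer-generated table to the intervention or control arm with a 1:1 allocation ratio".
- **Sample size calculation:** after the cluster inflation and a 10% drop-out allowance, "the final sample size was rounded to 300 per arm and 15 clusters". Numbers analyzed plans for 30 clusters and no fewer than 300 indoor smokers per arm.
- **Randomisation:** "A simple randomisation will be undertaken of the selected slums in the urban and peri-urban areas to receive intervention or not". The sequence is to be produced by computer. The Implementation paragraph again calls the method simple randomisation. No blocking, stratification or constraint is mentioned.
- **Allocation concealment:** "the allocation will be done after the baseline survey assessment by a statistician not directly related to the study". All indoor smokers are to be selected before the clusters are randomised.
- **Baseline data:** results will be shown for clusters and individuals because "the risk of chance imbalances are greater with clusters".
- **Outcomes and estimation:** arms are compared at baseline, and relevant factors found unbalanced enter the final analysis. The bulleted analyses that follow plan a comparison of end-of-follow-up cotinine adjusted for its baseline value, by linear mixed model or GEE.

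**The concern.** In standard usage, simple randomisation is an independent draw for each unit. It is 1:1 in expectation but does not fix the arm sizes, whereas the sample size and the planned numbers analysed both assume 15 clusters per arm.

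The second issue remains even if the split is fixed. The slums mix urban and peri-urban areas, and cluster size is assumed to vary widely (CV 0.45). Both features are known for all 30 slums when the statistician allocates, and neither enters the allocation. The protocol recognises the risk of imbalance and deals with it in the analysis. For factors other than baseline cotinine, that means choosing covariates after looking at the arms, with no stated criterion for what counts as unbalanced. This makes the model data-driven, and it cannot restore the number of clusters per arm.

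At stake are the precision and face credibility of the primary comparison, not its validity. The remedy is available only before allocation.

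**Working it through.** **Inputs (Sample selection; Sample size calculation).** 30 clusters, 15 per arm; mean size m = 20; CV = 0.45; ICC = 0.06; 113 per arm under individual randomisation; 80% power; two-sided alpha 0.05; 10% drop-out. No SD for cotinine is given.

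**1. The plan's own figure.** VIF = 1 + ((1 + CV²)m − 1) × ICC = 1 + (1.2025 × 20 − 1) × 0.06 = 2.383 (stated 2.4). Then 113 × 2.4 = 271.2 (stated 271); 271/20 = 13.6, so 14 clusters; 271/0.9 = 301.1 (stated 300). The sizing reproduces, and it rests on 15 clusters per arm.

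**2. Split under independent draws, Binomial(30, 0.5).** P(15 v 15) = C(30,15)/2³⁰ = 0.144.

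| Split, or more uneven | Probability |
|---|---|
| 13 v 17 | 58.5% |
| 12 v 18 | 36.2% |
| 11 v 19 | 20.0% |
| 10 v 20 | 9.9% |

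An arm of 12 clusters would expect 12 × 20 = 240 smokers against the planned 300.

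**3. Power by split.** The standardised effect implied by 113 per arm is (1.960 + 0.842) × √(2/113) = 0.373. With 18 analysed per cluster (20 less 10%), VIF = 1 + (1.2025 × 18 − 1) × 0.06 = 2.239. With SE = √[VIF × (1/n₁ + 1/n₂)], the normal approximation gives:

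| Split | Power |
|---|---|
| 15 v 15 | 82.5% |
| 13 v 17 | 81.8% |
| 12 v 18 | 81.0% |
| 10 v 20 | 77.9% |
| Average over all splits | 81.1% |

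The loss against 15 v 15 is about 1.5 points at 12 v 18 and 4.6 points at 10 v 20. A t reference on 28 degrees of freedom lowers the level (79.8% at 15 v 15, 78.2% at 12 v 18) but leaves the loss at 12 v 18 about the same.

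**4. Covariate balance with the split fixed at 15 v 15.** The arm difference in a cluster-level covariate has SD √(2/15) = 0.365 cluster SDs. P(|difference| > 0.5 SD) = 2 × [1 − Φ(0.5/0.365)] = 17.1%.

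For cluster size, one SD is 0.45 × 20 = 9 smokers. Half an SD is 4.5 per cluster, or 15 × 4.5 = 67.5 smokers between arms. With 600 in total, that is about 334 v 266.

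**The case against.** The strongest reply is that the text can be read as an unstratified draw of exactly 15 from a closed list of 30. The 1:1 ratio, the 15 clusters per arm, and a single allocation by one statistician after baseline all fit that reading, and simple is sometimes used to mean unstratified. This stands as a possibility. A reader might infer that the named method cannot give 1:1, but the documents support only that it is not guaranteed. The probabilities in step 2 apply to independent draws alone.

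A reader might also infer that the trial becomes underpowered. The figures do not show this: the average over all splits is about 81% by the normal approximation, close to the 82.5% at 15 v 15.

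Nor are baseline data ignored altogether. Cotinine is adjusted for its baseline value whether or not imbalance is seen. That covers the most prognostic variable but not location or cluster size.

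The 17% is for one covariate in cluster-level SDs and should not be multiplied across several as if they were independent; the document gives no basis for that. On the individual scale it is smaller: at ICC 0.06, half a cluster SD in cotinine is 0.5 × √0.06 = 0.12 individual SD. Chance imbalance is also already allowed for in the test size and confidence interval of a valid randomised comparison.

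Finally, cotinine is a baseline measure (Table 1), but nothing says that assay results for all 30 slums will be ready before allocation. The document also gives no urban and peri-urban counts, so the practicability of strata cannot be judged from it.

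**Conclusion.** The point holds in a limited form. The named method does not secure the 15 clusters and 300 participants per arm on which the plan relies: as independent draws, 15 v 15 occurs 14.4% of the time and 12 v 18 or worse 36% of the time. The direct power loss is small.

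The better reason to act is balance. Even with 15 v 15 fixed, each unrestricted cluster-level covariate has about a 17% chance of differing by more than half a cluster SD, and two relevant factors known at allocation are left to chance. Later adjustment for them is data-driven.

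These figures rest on equal-probability independent draws (step 2), the protocol's ICC, CV and mean size, an effect size back-calculated from 113 per arm (step 3), and a normal approximation (steps 3 and 4). The trial remains valid as written. This is an improvement that should be made before allocation, and Study status, which reports baseline collection as ongoing, indicates there was still time.

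**What to change.** 1. State that exactly 15 clusters go to each arm, and replace the term simple randomisation with the actual procedure.
2. Use stratified or covariate-constrained allocation on urban or peri-urban location and number of indoor-smoking homes. Add cluster mean baseline cotinine only if assay results for all 30 slums are available before allocation.
3. Keep the set of acceptable allocations large, and have the allocating statistician draw one from it at random.
4. Prespecify these factors in the primary model alongside baseline cotinine, in place of selecting them after a balance check.

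The cost is a little statistician time, revised wording and a few cluster-level terms in the model. It is not free: only the chosen factors are balanced, too tight a constraint shrinks the set of possible allocations, and waiting for cotinine assays could delay allocation, which is why that factor is conditional.

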*Ethical issues*: Any adverse events will be recorded and reported to the Chair of the Trial Steering Committee and the Chair of the Ethics Committee. Institutional Ethical Committee approval has been obtained vide letter dated 18-10-2022 from Amrita Institute of Medical Sciences (IEC-AIMS-2022-COMM-284). The protocol V2 was submitted and approved by ethical committee vide above. Informed consent and assent will be obtained from the respective participants by the coordinator of the study. The investigators will only have access to the data.
*Dissemination*: A dissemination will be carried out in Kochi with the participation of all stakeholders. The results of the study will be disseminated to all the stakeholders including the community, state and district NCD control officers. Following this the results will also be disseminated through publication.
*Public involvement*: The local self-government has been taken into confidence and they are fully supportive of this venture. Local steering committees have been formed in the intervention clusters to guide and support the intervention.

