### Study status

Currently the baseline data collection is ongoing.

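### The protocol conflicts on whether arms were known before enrolment closed: it randomises after baseline, denies allocation concealment, and reports committees already formed in intervention clusters during baseline

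*Protocol article*

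**What the plan says.** All references are to the protocol article.

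- **Sample size calculation, under Randomisation (Allocation concealment).** On timing and responsibility: "the allocation will be done after the baseline survey assessment by a statistician not directly related to the study". On order: "All the indoor smokers will be recruited and they will be selected before randomising clusters". Between these two statements stands "There is no allocation concealment". The Implementation paragraph that follows again places randomisation after the baseline survey. On who recruits, it says "the investigators will enrol the participants".
- **Intervention.** On consent: "Consent will be obtained during baseline survey and also before intervention at the local self-government level". The baseline survey is therefore the enrolment period.
- **Intervention, in the text after Figure 1.** In the future tense: "In the intervention clusters, an air quality monitoring committee will be formed to support the intervention".
- **Outcomes, under Public involvement.** As something already done: "Local steering committees have been formed in the intervention clusters to guide and support the intervention".
- **Study status.** "Currently the baseline data collection is ongoing".

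**The concern.** In a cluster trial the usual threat to comparability is recruitment by people who know the arm. They may search harder, persuade more or skip more households in one arm than in the other. Recruiting everyone before the clusters are randomised is the standard defence, and it is the only one this protocol offers, since it disclaims concealment in so many words. If intervention clusters could be named while households were still being found and consented, that defence is gone for those clusters.

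Several features of this trial would let such knowledge matter:

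- Eligibility turns on a man smoking inside the home, which is largely a reported behaviour.
- The woman who gives urine may be the spouse, another close female relative, or whichever woman spends longer at home. This leaves some discretion over whose cotinine, the primary outcome, is measured.
- The Training section has self-help group members, ASHAs and health workers carry out the baseline survey. Self-help group members and ASHAs also deliver the intervention.
- The Blinding paragraph says blinding may not be possible for investigators and frontline workers. Only the outcome collectors are said to be blinded.

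**Working it through.** No arithmetic decides this point. It rests on the order of three events: enrolment, allocation, and committees being set up in one arm.

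**Step 1. When is enrolment open?** Consent is taken at the baseline survey (Intervention), and baseline is unfinished at the time of writing (Study status). Enrolment was therefore open in at least some clusters.

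**Step 2. When can a cluster first be called an intervention cluster?** Under Randomisation, only after the baseline survey. At the time of writing, no cluster should yet have had an arm.

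**Step 3. What does the committee sentence require?** Public involvement reports committees already in place in the intervention clusters. Read literally, at least some clusters had an arm by then. The planned split is 15 and 15 of 30 clusters, so anyone who knew all the intervention clusters would also know all the control clusters.

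**Step 4. Set the possible readings side by side.**

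| Reading | Were arms known during enrolment? | What must change |
|---|---|---|
| The Randomisation order was followed and the committee sentence is loosely worded | No | The committee sentence, and the denial of concealment, because fixing participants before the draw largely prevents identification bias |
| The committee sentence is literal | Yes, in some or all clusters | The Randomisation order, which was not followed; the affected clusters need disclosure |
| Arms were released cluster by cluster as each roster closed | Not within a closed cluster | The Randomisation text, which describes no such release |

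Under every reading at least one current sentence is wrong or incomplete, and the reader cannot tell which.

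**Step 5. Can the consequence be sized?** Not from this document. It gives no randomisation date, no count of clusters whose arm was known, and no figure for how the households at issue would differ.

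**The case against.** The strongest reply is that the protective order is stated clearly and repeatedly. The Randomisation text gives it three times: allocation after baseline, smokers selected before the draw, and randomisation after the survey again under Implementation. It also names a statistician outside the study. Against this stands one sentence in the past tense.

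Tense is not reliable in this article. The Introduction reports FEV1/FEV6 as measured although follow-up measurements lie ahead, and the training booklet is described as developed and, a few lines later, by what it will contain. The Training section labels the survey clusters by arm when planning the baseline. The committee foreseen in the Intervention section has nearly the same function as the one reported as formed, and it is still in the future. The sentence under Public involvement may therefore be loose wording or concern another body.

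Room for selection is also limited. The survey is door to door and is meant to recruit every indoor smoker, so staff do not pick a sample. Refusals and missed homes remain possible.

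Most of this stands. A reader might infer that the arms were in fact known and that recruitment was biased. The document does not show that. A reader might also want to convert the risk into an inflated type I error. That would need an invented share of altered households and an invented cotinine shift. It would also ignore the planned comparison of follow-up cotinine adjusted for its baseline value, which removes much of a difference in level already present at enrolment. Adjustment does not reach selection on unmeasured traits, such as willingness to change, but the document offers no way to size what remains.

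What the reply does not remove is the conflict itself. If the protective order is true, the denial of concealment misdescribes the design and the committee sentence is wrong.

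**Conclusion.** The point holds as an internal contradiction on the trial's main safeguard against recruitment bias. It does not hold as proof that arms were known. The Randomisation text conflicts with Public involvement and Study status, and the committee sentence also sits badly with the future-tense committee in the Intervention section.

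The conclusion rests on two readings of the text: that the baseline survey is the enrolment period, which the consent sentence supports, and that the intervention clusters under Public involvement are the randomised intervention arm. If that sentence means something else, the risk falls away, but the text still needs correcting. No size in ng/ml or in error rate is claimed. What is affected lies anywhere between no cluster and all 30. It should be settled while baseline is open, because enrolment that closes with the arms known cannot be repaired afterwards. The Figure 1 flow diagram was not available for this check.

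**What to change.** 1. Reconcile the Randomisation text, the committee paragraph in the Intervention section, Public involvement and Study status. State when the sequence was or will be generated, when it was or will be released relative to the close of baseline, and who holds it. The statement should report what was actually done.
2. If the sequence has not been released, replace the denial of concealment with a rule: the independent statistician withholds the sequence until the baseline rosters and urine samples of all 30 clusters are complete and locked. Committees in intervention clusters are formed only after that. Correct or explain the sentence saying that they already exist.
3. If any cluster's arm was known before its roster closed, list those clusters. Add a sensitivity analysis of the primary outcome that excludes households enrolled after the arm was known.

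Cost: items 1 and 2 are a change of wording and a hold on the list until the last baseline cluster closes, with no extra staff or participants. Item 3 applies only if arms were known early. It needs the enrolment date of each household and the date on which each cluster's arm became known, and it loses some precision through the excluded households.
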